## Abstract

**Background:**

There is a need for more resources to support the cognition and quality of life of people with dementia. The individual cognitive stimulation therapy (iCST) app aims to provide cognitive stimulation and social interaction to people with dementia and carers through interactive touchscreen technology. The iCST app has been developed according to the principles of CST and iCST, which have previously shown to improve the cognition and quality of life of people with dementia and benefit the relationship between the person with dementia and his/her carer. The iCST app has also shown to improve the quality of the carer’s life.

**Objective:**

The aim of this study is to evaluate the usability of the iCST app intervention and the feasibility of conducting a full-scale randomized controlled trial (RCT) to assess the clinical effectiveness of the iCST app intervention compared to that of treatment-as-usual for people with mild-to-moderate dementia.

**Methods:**

We aim to recruit 60 people with mild-to-moderate dementia and their informal carers as dyads in a multi-center feasibility RCT with a treatment-as-usual control group. Both parties must be able to provide informed consent and participate in the intervention. Dyads will complete a baseline assessment that will include cognition and quality of life measures and they will subsequently be randomized (1:1) to the iCST app intervention in addition to usual care or to usual care only. All participants will be followed up at 5 weeks and at 11 weeks after the baseline assessments. A range of feasibility outcomes will be assessed, including recruitment and retention rates, intervention fidelity and usability, and acceptability of the outcome measures. A sample of the experimental group will be invited to a semistructured posttrial interview to further examine the experience of using the iCST app.

**Results:**

This study received funding in May 2015 and obtained ethical approval in March 2018. Data collection began in November 2018 and was completed in March 2020 with a total of 61 dyads recruited. Data analyses are in progress and the final results are expected to be available in the spring of 2021.

**Conclusions:**

This study will investigate whether it is feasible to conduct a full-scale RCT to evaluate the clinical effectiveness of the iCST app in comparison to that of usual care alone. In addition, this study will examine the usability of the iCST app. The data will provide information on potential modifications to be made to the intervention, study design, and study process.

**Trial Registration:**

ClinicalTrials.gov NCT03282877; https://clinicaltrials.gov/ct2/show/NCT03282877

**International Registered Report Identifier (IRRID):**

DERR1-10.2196/24628

## Introduction

### Background

Dementia poses a significant challenge to individuals in staying mentally stimulated and engaged. This is further exacerbated, given the lack of resources to support the cognition and quality of life (QoL) for people with dementia. Cognitive stimulation therapy (CST) is a nonpharmacological group treatment, which is strongly recommended by the National Institute for Health and Care Excellence. A previous randomized controlled trial (RCT) showed that CST can benefit the cognition and QoL of people with dementia [1]. The individual CST (iCST) intervention is delivered by a carer at home and has shown improvements in the relationship quality between the person with dementia and his/her carer and in the QoL of the carers [2].

Technology can improve accessibility to interventions by offering interventions on devices such as desktop computers and touchscreen tablets. For instance, in light of the COVID-19 pandemic wherein CST groups for people with dementia were unavailable, Cheung and Peri [3] found that it was feasible to offer virtual CST groups by using Zoom, a video conferencing software. This platform may support people with dementia to stay mentally stimulated and engaged in the safety of their homes. Touchscreen interventions, in particular, can have an array of benefits, as touchscreen platforms can be intuitive and therefore, have a high level of acceptance among people with dementia [4]. A systematic review has shown that touchscreen interventions with sound designs and tailored content can improve the well-being of people with dementia [5]. Moreover, these interventions can have a positive impact on the well-being of carers by decreasing their burden and improving the quality of the relationship with the person they are caring for by spending more time together. An example is the Computer Interactive Reminiscence and Conversation Aid (CIRCA) program, which offers computerized cognitive stimulation by prompting reminiscence among people with dementia supported by a wide range of multimedia stimuli on a touchscreen computer system. When used in a group setting, it can lead to improvements in both the cognition and QoL of people with dementia [6]. Researchers also found that CIRCA could positively benefit the relationship quality of the person with dementia and his/her carer when using the program together [7]. However, despite these encouraging findings, the field of computerized cognitive stimulation is underdeveloped [8], and high-quality studies involving carer-delivered computerized cognitive stimulation programs, in particular, remain scarce. More research in this field is warranted as the existing evidence seems to be promising; there are minimal risks in engaging with computerized cognitive stimulation and such interventions could potentially be cost-effective. Therefore, researchers have developed a novel, touchscreen iCST app, which aims to offer cognitive stimulation to people with dementia and can be used at home with carers. Rather than using a touchscreen computer system like CIRCA, the iCST app has been developed as a native app; thus, it can be downloaded from the App Store and Google Play stores on touchscreen tablets, which further improves the accessibility of the intervention. Like CIRCA, the iCST app aims to stimulate conversation between the person with dementia and his/her carer by using a range of topics, which can include reminiscence. However, the iCST app also offers other types of activities supported by multimedia stimuli in order to target specific cognitive functions such as memory and language. It is hoped that the iCST app may produce combined benefits of engaging in CST, iCST, and touchscreen technology. The app’s development followed the Medical Research Council Framework for developing complex interventions and the Centre for eHealth Research roadmap [9,10]. This included extensive reviews of CST and iCST materials and end-user involvement through informal consultations, focus groups, individual interviews, and usability questionnaires [11]. The next stage of development encompasses this feasibility RCT. Findings from this study will inform whether a large-scale RCT evaluating the clinical effectiveness of the iCST app is indicated by investigating relevant study parameters related to the study design and process.

### Study Aim

The aim of this study is to evaluate the usability of the iCST app intervention and the feasibility of conducting a full-scale RCT to assess the clinical effectiveness of the iCST app intervention compared to that of treatment-as-usual (TAU) for people with mild-to-moderate dementia.

## Methods

### Study Design

The 26-item CONSORT checklist of information to include when reporting feasibility trials will be used for this study to ensure that all the necessary and relevant information is reported [12]. This study was registered with ClinicalTrials.gov on July 19, 2017 (registration number: NCT03282877). This study is a multi-center, feasibility RCT with an allocation ratio of 1:1. People with dementia and carers will be recruited as dyads and will be randomized to either the experimental (completing 30-minute iCST app sessions twice or thrice per week) or the TAU control group for 11 weeks. Dyads will complete the baseline assessment prior to randomization and thereafter, the first follow-up will be completed at 5 weeks after the baseline assessments and the second follow-up at 11 weeks after the baseline assessments (Figure 1). A sample of the experimental group will be invited for semistructured posttrial interviews to gain insights into the acceptability of the iCST app, including the experience of using the app and any facilitators and barriers for implementation in daily life.

**Figure 1 figure1:**
[figure not shown]
Flow diagram for the feasibility randomized controlled trial of the individual cognitive stimulation therapy app. FU1: first follow-up; FU2: second follow-up; iCST: individual cognitive stimulation therapy.

### Participants

Recruitment started on November 1, 2018 and is conducted in 5 secondary care settings in England: Derbyshire Healthcare National Health Service (NHS) Foundation Trust, Leicestershire Partnership NHS Trust, Lincolnshire Partnership NHS Foundation Trust, Northamptonshire Healthcare NHS Foundation Trust, and Nottinghamshire Healthcare NHS Foundation Trust. In addition, participants will be identified through a variety of settings, including general practitioner practices, community mental health teams, memory clinics, care homes, memory cafes, support groups, and voluntary sector organizations such as the Alzheimer’s Society. Remote recruitment will include registration on the website Join Dementia Research, publicizing the study using social media platforms such as Twitter, and the distribution of information leaflets and posters to organizations and professionals involved in the identification of possible participants.

### Eligibility Criteria

The sample will include people with mild-to-moderate dementia and their informal carers (relatives or friends). The inclusion and exclusion criteria were adapted from previous CST and iCST research studies [1,2] and are shown in Textbox 1.

Inclusion and exclusion criteria for people with dementia and for their carers in this study.
**Inclusion criteria**
For people with dementiaMeet Diagnostic and Statistical Manual of Mental Disorders (DSM-IV) criteria for dementia [13].Score 10 or above on the Mini-Mental State Examination [14] or score of 16 or above on the Montreal Cognitive Assessment [15], where available.Some ability to communicate and understand (eg, ability to give informed consent).Ability to speak and understand English.See/hear well enough to participate.No major physical illness or disability affecting their participation.Age range: 50 years–no maximum age limit.Availability of a touchscreen tablet for the person with dementia and for the carer.Availability of a carer (or relative/friend) to participate in the activities.For carersMinimum age: 21 years.Ability to speak and understand English.See/hear well enough to participate.No major physical illness or disability affecting their participation.
**Exclusion criterion for people with dementia and for carers**
Concurrent participation in any other interventional study.

### Sample Size

A formal sample size calculation is not appropriate for a feasibility trial. A previous audit of trials registered in the Clinical Research Network database in the United Kingdom found that most feasibility and pilot trials had a median of 30 or 36 participants per arm and the researchers recommend an upper limit of 60 participants for a feasibility trial [16]. Therefore, a target of 60 dyads is set for this study, leading to 30 dyads per treatment arm.

### Procedure

#### Screening for Eligibility

Anticipating logistical support from the National Institute for Health Research Clinical Research Network East Midlands, we expect that staff members at each research site will check the eligibility of referrals received from clinicians and staff at the recruitment sources. Participants fulfilling the inclusion criteria will be sent a participant information sheet containing full details about the study. If the dyad is interested in participating, they will be recruited into the trial and a date for the baseline assessment and consenting will be set by the Clinical Research Network staff member.

#### Randomization

Randomization will take place after consent and the baseline assessments by using a web-based central randomization service called Sealed Envelope [17]. Block randomization will be employed with block sizes of 4 to 6 (randomly varied and generated by Sealed Envelope), which is a useful method for small sample sizes to allocate an equal number of participants to each treatment arm [18]. The researcher at the local site will perform each randomization using the participant identification code of the person with dementia only. The allocation to the experimental or TAU control group will automatically apply to the carer as well. Dyads will be informed of their allocation outcome over the telephone and, if necessary, a visit will be arranged for dyads in the experimental group to install the iCST app.

#### Blinding

This trial will include both blinded and unblinded researchers at each local site. It is not possible to blind the participants to their treatment arm as the iCST app is a nonpharmacological intervention. However, each study site will include at least one researcher kept in ignorance of study allocations. The baseline assessment can be performed by either researcher. However, both follow-ups will be completed only by the researcher who is unaware of the randomization outcome for each dyad. If disclosure does occur, this will be recorded by the visiting researcher along with details on how it occurred. The unblinded researcher will perform the randomization, communicate the outcome with the participants, and for the experimental group, install the iCST app, provide weekly telephone support calls, and complete the usability and acceptability questionnaire at the end of the study. Furthermore, the unblinded researcher will not be informed about the results of the assessments.

### iCST App Intervention

Participants in the experimental group will use the iCST app (prototype v3.0) over 11 weeks after the baseline assessments. The content of the app was modified from the paper-based iCST manual, including the principles, themes, and activities [2], and was based on consultations and qualitative research with people with dementia, carers, and the software development company [11]. The iCST app is a one-to-one, carer-led, home-based program of structured cognitive stimulation for people with dementia but delivered on a touchscreen tablet. It includes 21 activities consisting of both game-like interactive features such as audio-visual stimuli and discussion questions (Table 1). These activities offer mental stimulation not only through the content on the app but also through conversation.

**Table 1 table1:** List of the individual cognitive stimulation therapy app activities (prototype v3.0).

Type of activity	Activity name
Games only	Being Creative Spaceman Trivia Quiz Word Search Sudoku Being Active Brainstorm
Discussion questions only	Past Events Useful Tips My Life Arts Old Wives’ Tales Toys Are Us
Games and discussion questions	Sounds Odd one Out The Price is Right Globe Trotter Food In Pairs Sayings ISpy

In addition, this app includes several other features such as a short introduction section explaining the background and key tips for using the app, a home screen that features completed activities, and a choice of 2 levels. Level 2 contains either more challenging content or different questions from Level 1, and it is up to the participants to determine which level they feel more comfortable with for each activity. Figure 2 contains screenshots of the iCST app. Considering previous CST and iCST research and findings from the development work, it is recommended that participants use the app for 2 or 3 times a week for 30 minutes [2]. Participants are free to spend more time on the app if they wish, and this will be recorded during the weekly telephone calls.

**Figure 2 figure2:**
[figure not shown]
Screenshots of the individual cognitive stimulation therapy app. A. home screen and B. sounds activity.

### Training and Adherence

In order to ensure treatment integrity for all participants, individual study sites will receive a demonstration of the iCST app along with training in its installation and use prior to the start of recruitment. Dyads in the experimental group will receive an in-home visit from the unblinded researcher who will install the app and explain how it works using a short supplementary document containing instructions with screenshots of the app. Furthermore, all dyads will receive weekly telephone support calls from the same unblinded researcher in order to monitor adherence and to track the overall progress and any challenges or technical difficulties with using the iCST app. Phone calls will be completed with the carer and all questions will be included on a standardized telephone sheet. The questions relate to general experience, number of sessions completed in a week (on average), amount of time spent per session (on average), enjoyment, and any likes/dislikes. Any reason for not being able to use the iCST app over the week will also be recorded on the telephone sheet.

### TAU Group

The control group will consist of the TAU group and will not receive any additional interventions. TAU groups are typically used to compare experimental interventions to care, which participants already receive in practice [19]. Therefore, the TAU control group will enable us to compare the effects of the iCST app with the natural progression of people with dementia under conditions of usual care. The treatments and services that are already available to people with dementia and their carers randomized to the TAU control group may differ between and within recruitment sites, for instance, regarding acetylcholinesterase inhibitors or being involved in some form of cognitive stimulation already. However, it is unlikely that people have access to computerized versions of iCST since these do not exist, to the best of our knowledge. The visiting researcher will record any current participation with CST groups and use of acetylcholinesterase inhibitors at the baseline assessment.

### Outcomes

#### Feasibility Outcomes

In order to determine the feasibility of conducting a full-scale RCT with the iCST app in the future, this trial will investigate key feasibility aspects, including the rates of recruitment, screening, randomization, and retention by using enrolment logs [9]. Acceptability of the outcome measures will be evaluated by assessing the completion rates, and the acceptability and fidelity of the iCST app will be evaluated through weekly telephone support calls, analytics, and a usability and acceptability questionnaire. It is expected that >75% of the participants in the experimental group will need to complete the recommended minimum of 2 activities on average every week for the iCST app to be considered feasible. This benchmark has been adopted based on work in some previous feasibility trials, including psychological treatments where benchmarks for successful adherence ranged between 75% and 80% [20,21].

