#### Clinical Outcomes

Previous CST and iCST research and the Interdem consensus statement on outcome measures for dementia informed the outcome measure selection for this study [22]. Key outcome measures of interest for people with dementia (Textbox 2) are cognition and QoL, as previous CST research has shown improvements in these domains [1]. For carers, the key outcome measure (Textbox 3) is QoL as previous iCST research has shown improvement in the QoL of carers [2]. This study additionally includes technology-related scales to assess the usability and acceptability of the iCST app and computer use self-efficacy (Textbox 4). All assessments will take place in the homes of the participants. Wherever possible, 2 researchers will visit the participants in order to interview the person with dementia and his/her carer separately. It will be possible to conduct the assessments over 2 days in case of fatigue or other practical issues such as lack of time. As in the previous iCST trial, the first follow-up at 5 weeks will be included to safeguard data against loss-to-follow-up [2]. The second follow-up will take place at 11 weeks after the baseline as this should be the point that participants in the experimental group will have completed each activity on the iCST app.

Outcome measures for people with dementia.

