### Statistical Analyses

Key feasibility outcomes will be reported through frequencies and will include the number of participants screened, recruited, randomized, and retained through the duration of the trial. Adherence to the intervention will be assessed by calculating the average number of iCST app activities completed by the dyad logged in the weekly telephone calls. The usability and acceptability of the iCST app will be further investigated by examining data from the weekly telephone calls, posttrial interviews, and by calculating scores on the Questionnaire of Usability and Acceptability, with higher scores indicating higher levels of usability and acceptability. Data from the posttrial interviews will be coded and summarized and may be analyzed thematically with specialized software if sufficient data have been obtained to reach data saturation [35]. Lastly, outcome measures will be assessed for appropriateness by calculating missing data rates within the measures and across the follow-ups. As this is a feasibility trial and null hypothesis significance testing is inappropriate due to a likely lack of power to detect significant effects of the intervention [36-38], analyses will mainly include descriptive statistics computed for each group and outcome measures, including means, standard deviations, 95% confidence intervals, and effect sizes [12,39]. However, in order to compare the outcomes on each of the questionnaires between the 2 groups, an analysis of covariance will be undertaken, which will help to better understand any trends in the data. All analyses will be based on the intention-to-treat principle in that all available data will be included in the analyses. Rules for missing data will be adapted from the main iCST trial [2]. Data will not be imputed if outcome measures or assessments are missing in full, and imputation (using prorating) will only be used when fewer than 20% of cases are missing on any given measure.

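### The only numeric feasibility benchmark counts activities, but the recommended dose and the listed call topics count sessions

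*Protocol article*

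**What the plan says.** Feasibility Outcomes gives one numeric criterion for the app: more than 75% of the experimental group "will need to complete the recommended minimum of 2 activities on average every week for the iCST app to be considered feasible". The 75% to 80% range cited next to it describes adherence benchmarks in earlier trials and is not a second criterion. Statistical Analyses assesses adherence by "calculating the average number of iCST app activities completed by the dyad logged in the weekly telephone calls".

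The dose is stated elsewhere, in another unit. Study Design describes the experimental arm as "completing 30-minute iCST app sessions twice or thrice per week". The iCST App Intervention section says "it is recommended that participants use the app for 2 or 3 times a week for 30 minutes". Under Training and Adherence, the questions on the standardized telephone sheet relate to general experience, "number of sessions completed in a week (on average), amount of time spent per session (on average), enjoyment, and any likes/dislikes". Feasibility Outcomes also names analytics as a source on acceptability and fidelity, without saying what they record.

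**The concern.** The benchmark appeals to a recommended minimum, yet the protocol recommends nothing in activities. The only recommendation with a minimum of two is in sessions, or occasions of use. The stated analysis needs an activity count from the calls, while the topics listed for those calls include sessions and minutes but no activity count. No section says how many activities make up a session.

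At stake is which dyads count as adherent on the one stated number that decides whether the app is considered feasible. Analyses were still in progress when the article was written, so an unsettled unit could be settled after the adherence data had been seen.

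**Working it through.** **1. Where the figure of 2 comes from.** There are two routes in the document.
- Dose: the recommended minimum is 2 uses a week. This gives 2 activities a week only if one use equals one activity.
- Content and timing: the app has 21 activities (iCST App Intervention), and Clinical Outcomes says of the 11-week visit that "this should be the point that participants in the experimental group will have completed each activity on the iCST app". The pace is 21 / 11 = 1.91 activities a week, close to 2.

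**2. What that pace implies per session.**
- At 2 sessions a week: 21 / (2 × 11) = 21 / 22 = 0.95 activities per session.
- At 3 sessions a week: 21 / (3 × 11) = 21 / 33 = 0.64.

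These ratios count first completions only. One activity per session fits the minimum dose well and the upper dose less well.

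**3. Converting the benchmark to the dose.** Let k be activities per session. The documents do not give k; 0.75 to 2 is an assumed range, and the row at 0.95 is the pace from step 2. Sessions needed for 2 activities a week = 2 / k. Minutes = 30 × 2 / k = 60 / k. The recommended minimum is 2 × 30 = 60 minutes.

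| k | Sessions a week needed | Minutes a week | Share of the 60-minute minimum |
|---|---|---|---|
| 0.75 | 2.67 | 80 | 133% |
| 0.95 (21/22) | 2.10 | 63 | 105% |
| 1 | 2.00 | 60 | 100% |
| 1.5 | 1.33 | 40 | 67% |
| 2 | 1.00 | 30 | 50% |

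The two units agree exactly only at k = 1.

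**4. The same dyad under both units.**
- k = 2, one session a week: 1 × 2 = 2 activities, adherent by activities; 1 session, not adherent by sessions.
- k = 0.75, two sessions a week: 2 × 0.75 = 1.5 activities, not adherent by activities; 2 sessions, adherent by sessions.

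**5. The threshold itself.** With the target of 30 app dyads, 0.75 × 30 = 22.5, so more than 75% means at least 23. This is the same in either unit; the unit only changes which dyads are counted.

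**The case against.** The strongest reply is that the meaning can be recovered. Only one recommendation in the protocol has a minimum of two, so the benchmark must point back to it, and the pace of 0.95 activities per session supports reading activity as session. This largely stands: it is probably what the authors meant, and it limits the likely effect. It does not remove the mismatch, because the app's activities are a distinct list of named items and nothing says that one of them fills a 30-minute session.

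A second reply is that the telephone sheet is not shown. The listed topics are a summary, Statistical Analyses says that activities are logged in the calls, and analytics may hold the count. This also stands. A reader might infer that the activity count cannot be obtained; the documents do not support that. They show only that the listed topics and the planned analysis use different units.

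A third reply is that the stakes are limited. The Discussion bases recommendations for a full trial on a checklist of many trial components, and recruitment, retention, completion rates, usability scores and interviews all contribute. That is correct.

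A fourth is that moving to sessions alters the only numeric criterion after data collection ended in March 2020. Reporting both rates and disclosing the change answers this.

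**Conclusion.** The point holds as an inconsistency of unit in a decision threshold, and it should be corrected. Its size depends on activities per session, which the documents do not give. Near 1 it is small: at 0.95 the benchmark asks for about 105% of the minimum dose. Over the assumed range of 0.75 to 2, it asks for between 133% and 50%.

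Several stronger readings are tempting and are not supported.
- That the benchmark in fact passes dyads on half the dose. This needs k = 2, which is an assumption. At that rate a dyad on the minimum dose would do 4 activities a week and could go through all 21 in 21 / 4 = 5.25 weeks, against the 11 that the protocol expects.
- That a dyad doing each activity once must fail because 1.91 is below 2. This depends on the weeks of use and on repeats not counting. The app is installed after baseline, and over 10.5 weeks the average is 21 / 10.5 = 2.00.
- That the verdict turns on one dyad. A single dyad at the boundary decides any threshold in an arm of 30, whatever the unit.
- That silence on repeats or second levels is an error. A journal article may leave such a counting rule to the full protocol.

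**What to change.** In Feasibility Outcomes and Statistical Analyses, state the benchmark as more than 75% of app dyads averaging at least 2 sessions a week, taken from the telephone sheet, and report mean weekly minutes beside it. Also report the rate under the activity count as published, naming its source (call sheet or analytics). Disclose that the unit was clarified after data collection. Make the change before adherence is computed, if that is still possible. The 11-week visit rationale in Clinical Outcomes needs no change.

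The cost is wording in two sections, one extra reported rate, and a disclosed clarification after data collection. Sessions and time per session are already listed call topics and analytics are already planned, so no new data, visits or participants are needed. The sample size is not affected.
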